#### Sample size estimation

The sample size calculation (drawing on previous literature) with an estimate of how many participants will be needed for the primary outcome to be statistically, clinically and/or politically significant. For the specific primary outcome of liver fat and microbiota, based on our plot study, 34 subjects in each group would have 85% power for mean comparison between the randomized groups for the liver fat. We set the significance level at 0.05 and allowed for 10 mean comparisons with the Bonferroni correction between the groups. Taking into account multi-variable comparisons in the analysis, we increase our simple size to 50 in each group. We also taking into account the compliance and drop-out (15%), thus the total number of subjects was estimated to meet each specific aim.

In addition, typical projection-based methods used to analyze whole-genome data, such as Principal Component or Partial Least Squares Regression, do not have statistical inference methods. Thus, the corresponding methods for sample size estimation are data-driven methods involving latent variables. However, the large dimension and the time series nature of our datasets provide a good opportunity for inferring associations between different measurements. By using a systems biological approach we can develop models based on path analysis, which comprehensively integrate data for analysis. With such models we will be able to reveal the relationships between different variables.

### Randomization methods

1. Randomization Process:

A computer program will be used for generating the randomization assignment for this study by a statistician. 10 blocks of 20 randomization numbers will be generated and sealed in an envelope and kept by the study coordinator. On the basis of subjects’ enrolment time when 20 qualified subjects are reached, the study coordinator will open one block to allocate subjects into one of the 4 groups (target 50 persons per group, see Figure 1):

2. Blinding:

1) Exercise group (AEx)

2) Diet group (LCh)

3) Exercise + Diet group (AEx + LCh)

4) Control group (Con)

In addition two references groups are not in randomization:

5) Pre-diabetes without NAFLD (Ref1)

6) Healthy reference group (Ref2)

Since lifestyle intervention is not possible for subjects to be blinded, we have designed the study in such way that the tests and analyses will be blinded for investigators during the study.

The study coordinator will be blinded from which group the participants are signed in. The accuracy of the randomization log is the responsibility of the study coordinator.

Investigators will be blinded with respect to the randomization assignment of each participant. The investigators will remain blinded until the completion of the study.

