At the second visit, a physician and a researcher will examine all the results of the first visit to verify that the subject meets the inclusion criteria. If a person is qualified for participation in the study, he or she will be invited to the laboratory at the Department of Sport Medicine, Shanghai University of Sport for demographic, health history and physical activity questionnaires, height, weight, waist circumference, blood pressure, physical performance, body composition by DXA, as well as instructions for fecal sample and 24 hours urine collections. They will be also invited to have a magnetic resonance spectroscopy (^1^H MRS) scan to evaluate whether they have NAFLD (>5% liver fat content). The qualification of the participants will be established after this visit and randomization will be performed.

4. Randomization visit:

When the qualified subjects are randomized, an information meeting will be organized for each group. Detail of the activities during intervention will be explained by a principle investigator or a co-principle investigator. For the AEx group, we will provide walking poles and teach them how to use it. A heart rate monitor (M5 Suunto Oy, Finland) will be provided during each exercise session to monitory the intensity and duration of exercise. For the LCh group, a dietary consultation will be organized to instruct subjects how to prepare their breakfast and dinner and what we are going to provide them for lunch during the intervention. In addition, we will provide a mobile phone to each subject and teach them how to take pictures of their breakfast and dinner. For the AEx + LCh group, we will provide instructions as abovementioned both for exercise and diet groups. For the control group and both reference groups, we will emphasize the importance of their participation in study and instruct them to maintain their habits during the intervention. All groups will be instructed to fill a daily diary regarding their daily activities and a step counter will be provided to them to monitory their daily walking status.

5. Follow-up visits:

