The purpose of the follow-up visits is to monitor the compliance, enhance retention of the subject in the study, and obtain information on factors that may affect outcomes of the study. After the randomization visit, a study coordinator will contact participants every month to check their exercise records and update the exercise program. The study coordinator will also give feedback of their dietary intake on the basis of the images of meals and snacks provided by the subjects themselves. The participants will have follow-up visits to the laboratory of Shanghai Sport University at months 3, 6, 12. Their height, weight, food frequency questionnaire, physical activity record, fitness tests, blood pressure, blood samples, fecal samples, urine samples and changes in health status will be checked at those time points. MRI and DXA will be included in the follow-up visits for months 6 and 12.

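### The protocol declares blinded the coordinator who allocates participants and the investigators who brief each arm; for those roles the claim is impossible and the sections must be reconciled

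*Protocol article*

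**What the plan says.** All references are to the protocol article.

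**Randomization methods, Randomization Process.** The sequence comes from a statistician: "A computer program will be used for generating the randomization assignment for this study by a statistician". Custody then passes to the coordinator: "10 blocks of 20 randomization numbers will be generated and sealed in an envelope and kept by the study coordinator". The trigger for opening a block is "On the basis of subjects’ enrolment time when 20 qualified subjects are reached", at which point "the study coordinator will open one block to allocate subjects into one of the 4 groups".

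**Randomization methods, Blinding.** Participants cannot be blinded, so the section relies on tests and analyses being blinded for investigators. It declares: "The study coordinator will be blinded from which group the participants are signed in". The next sentence makes the coordinator responsible for the accuracy of the randomization log. Investigators are said to be blind to each participant's assignment, and "The investigators will remain blinded until the completion of the study".

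**Measurements procedures, Randomization visit.** Each randomized group has its own information meeting. "Detail of the activities during intervention will be explained by a principle investigator or a co-principle investigator".

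**Measurements procedures, Follow-up visits.** After randomization "a study coordinator will contact participants every month to check their exercise records and update the exercise program". The coordinator also comments on participants' diet from their meal images.

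**The concern.** Blinding is claimed for two roles, and the procedures in the same article give both roles knowledge of the arm. Carried into the trial report, the claim would describe a protection that the trial did not have.

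This matters because the article presents blinding on the investigators' side as its answer to the unavoidable lack of participant blinding. Some outcomes can be influenced by a tester who knows the arm: the 2 km walk, the step test, the maximal contractions and the questionnaires, all listed as secondary, and the semi-automatic segmentation of abdominal fat. A reader needs to know which people were really blind when those were measured.

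A second, smaller issue is that the person who holds the allocation list also opens it, applies it to 20 already identified participants and certifies the log.

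**Working it through.** The only arithmetic is the block structure, and it agrees: 10 blocks × 20 = 200 = 4 groups × 50. If blocks are balanced, which the article does not state, each holds 20 / 4 = 5 participants per arm. The rest is a comparison of roles.

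**1. Coordinator, within Randomization methods alone.**

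| Task or status | Knows the arm? |
|---|---|
| Keeps the sealed numbers | Not while sealed |
| Opens the block and allocates the 20 participants | Yes |
| Answers for the accuracy of the log | Yes |
| Declared status: blinded to group | No |

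The second and third rows cannot hold together with the fourth. No other section is needed to show this.

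**2. Coordinator, after randomization.** Follow-up visits gives a study coordinator the monthly exercise update and the comments on meal images. Only AEx and AEx + LCh have an exercise programme to update. Under Randomization visit, only LCh and AEx + LCh receive phones for photographing meals. Knowing both items separates all four arms:

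| | Meal photographs | No meal photographs |
|---|---|---|
| Exercise programme | AEx + LCh | AEx |
| No exercise programme | LCh | Con |

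Whoever does this monthly work learns the arm without seeing the list.

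**3. Investigators.** The promise covers each participant's assignment, lasts until completion and exempts nobody. The Randomization visit text has a principal or co-principal investigator explain the activities at meetings organized by arm. Assuming that the speaker can see who attends, the speaker knows those participants' assignment from that day.

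**4. Other staff.** The section on ethical issues says samples are coded by ID. Nothing in the article shows that laboratory, imaging or analysis staff learn the arm. The contradiction does not reach them.

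**5. Concealment.** The safeguards stated are:
- a statistician generates the list;
- the blocks are sealed;
- a block is opened only when 20 participants have qualified;
- allocation goes by enrolment time;
- baseline assessment comes before randomization (Trial design).

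Eligibility is thus settled before any assignment in that block is revealed. What remains is that not opening early, and keeping to enrolment order once the block is open, depend on the same role that keeps the log. No second person is described as checking either.

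**The case against.** The strongest defence is that the working commitment is blinding of tests and analyses, and nothing shows that to be broken. Samples carry IDs, exercise and diet are delivered largely by an instructor and a nutritionist, and an article may leave a list of blinded assessors to the full protocol. The primary outcomes are largely instrument-based: spectra fitted by software, an automatic analyzer, automated DNA extraction and sequencing. This stands. A reader might infer that the trial has no blinding at all; the article does not support that, and the lack of a named assessor list is not a finding here.

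A reader might also infer that concealment has failed and that every comparison is biased. That does not follow either. An allocator who knows the assignment after opening a block is not in itself a concealment failure, and steering enrolment by predicting the next assignment is largely closed off. The remaining risk needs a deliberate departure from procedure, which nothing in the article suggests.

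The coordinator's later role is less settled than Follow-up visits makes it look. That section begins with an indefinite article, so there may be more than one coordinator. The section on concomitant adherences assigns monthly diet feedback to the nutritionist, and the questionnaire section assigns feedback to the family doctor. If a second person makes the monthly contacts, step 2 no longer bears on the allocating coordinator, but step 1 is unaffected.

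Finally, the coordinator sentence might mean blind until the block is opened. That would describe concealment, not blinding; the sentence sets no such limit and stands under Blinding.

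**Conclusion.** The point holds for two roles. Blinding is impossible for the coordinator who allocates, on the Randomization methods text alone, and for any investigator who briefs an arm, on the assumption in step 3. It is neither shown nor disproved for laboratory, imaging and analysis staff.

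On concealment the conclusion is limited: the safeguards are genuine, but custody, opening, allocation and log sit with one role without a stated independent check, across all 10 blocks and 200 randomized participants.

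The size of any bias cannot be derived from the document. The outcomes most open to a tester's knowledge are secondary. What is certain is that a stated bias-control measure cannot be carried out as written and should not be reported as it stands.

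**What to change.** 1. Reconcile Randomization methods with the Randomization visit and Follow-up visits text, including whether the allocating coordinator is the person who makes the monthly contacts.

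2. Replace the blinding statement. Say that participants, the allocating coordinator, the intervention staff and any investigator who briefs an arm are not blinded. Claim blinding only for staff who acquire or process outcome data and for the analyst, working from ID codes or coded arms, and only where they have no delivery or briefing role. Where a tester also delivers or briefs, say so.

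3. For blocks not yet opened, let the statistician keep the list. The coordinator submits the 20 IDs in fixed enrolment order and the statistician returns the 20 assignments.

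4. For blocks already opened, report the procedure actually used. Under Trial status, interventions began in March 2013 and recruitment runs to June 2014, so new custody can apply only from here on.

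The cost is a short turnaround per block and a less favourable blinding statement. The statistician is already in the trial, and limiting the claim to staff who are in fact separate requires no new posts.

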### Statistical methods

All data collected by questionnaires will be entered into database management software (Filemaker Pro version 10, FileMaker Inc. Santa Clara, CA, USA), double checked by independent researchers, and exported to PASW statistics version 20 (IBM Corporation, USA). If data is not normally distributed, their natural logarithms will be used for further analysis. Descriptive statistics will be used to present the background and anthropometric data at the baseline and follow-up assessments as mean and 95% confidence interval (CI) unless otherwise stated.

An intention-to-treat (ITT) analysis will be performed to compare the AEx, LCh and AEx + LCh groups to Con group. The effects of the interventions will be assessed using analysis of variance (ANCOVA) for repeated measures (treatment group × time) and baseline difference as a covariate. If the significance of the group by time interaction is p < 0.05, the effect will be localized utilizing Bonferroni for multiple comparisons. The level of statistical significance chosen for the contrasts will be p < 0.05. In addition to the ITT analysis, efficacy or active treatment analysis will be done when the compliance of the participation of the intervention is ≥60% of the whole trial and for <60% not more than 3 months continuously [ANCOVA for repeated measures (treatment group × time) and baseline difference as a covariate.] The percentage differences (0–6month) will be calculated from duration between baseline and end point measurements for each individual. The comparison of percentage changes in different groups will be performed using ANCOVA (two factor interactions: compliance/noncompliance × treatment group) controlled for the baseline value using Bonferroni for multiple comparisons. If the significance of the overall group difference is p < 0.05, then the effect will be localized by contrast to the Con group. When the 95% CI does not include zero, the difference is regarded as statistically significant at α = 0.05.

Linear Pearson’s correlation, partial correlation, Kendall Tau’s, and bivariate, logistic, and multivariate regression analysis will be used for analysing relationships. In addition, systems biology approaches will be used to develop models which integrate the different types of data and the high-throughput data measured in terms of gut microbiota composition and fecal SCFAs content, as well as LPSs and inflammation.

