### Primary and secondary outcomes

#### Primary outcomes

1. Liver fat content

2. Serum metabolomics, level of glucose, insulin, triglycerides and free fatty acids

3. Gut microbiota composition

The measurements of liver fat content, variables related to glucose metabolism, triglycerides and free fatty acids will be assessed at baseline and 6-month follow-up; gut microbiota composition will be measured at baseline, 3-month and 6-month time points.

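### Arm comparisons are gated on a group-by-time interaction whose time levels are not defined; on one natural reading the gate cannot detect a stable effect

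*Protocol article*

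**What the plan says.** Statistical methods in the protocol article fixes three things.

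- **Comparison:** "An intention-to-treat (ITT) analysis will be performed to compare the AEx, LCh and AEx + LCh groups to Con group".
- **Model:** "The effects of the interventions will be assessed using analysis of variance (ANCOVA) for repeated measures", with treatment group × time, "and baseline difference as a covariate".
- **Decision rule:** "If the significance of the group by time interaction is p < 0.05, the effect will be localized utilizing Bonferroni for multiple comparisons".

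The section does not say which visits form the time factor, or at which visit the arms are then contrasted. It also describes an ANCOVA of 0–6 month percentage change. That analysis has compliance and treatment group as factors, is controlled for the baseline value, and contrasts arms with control only if the overall group difference is significant.

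The visits themselves are not settled. Primary outcomes puts liver fat, glucose variables, triglycerides and free fatty acids at baseline and 6 months, and adds that "gut microbiota composition will be measured at baseline, 3-month and 6-month time points". The follow-up visits item of Measurements procedures puts blood and faecal samples at months 3, 6 and 12, and MRI at months 6 and 12.

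**The concern.** A group-by-time interaction means different things depending on whether baseline is a level of time. With baseline among the levels, it asks whether the arms changed differently from baseline, which is the treatment effect. With baseline moved out to be the covariate and only post-baseline visits left, it asks whether the treatment effect differs between those visits. An effect present at the first follow-up and held at the next is then invisible to the gate, and the rule forbids the contrasts that would show it.

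A held effect is plausible here. Under Interventions, the diet programme aims for a set weight loss in the first 3 months, then for maintenance with gradual further reduction. The same sentence in the plan could therefore yield either a well-powered comparison of the arms or almost none, and the choice could be made after the data are seen.

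**Working it through.** **Inputs.** From the article: 4 randomised arms, 50 per arm, 15% drop-out, so 50 × 0.85 = 42.5, taken as 42 per arm. Assumed, because the article gives none: the standardised effect d, and a correlation r between any two visits. The follow-up schedule's MRI entry is taken to include the spectroscopy that yields liver fat.

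**1. The plan's own figure.** It states 34 per group for 85% power, with alpha 0.05 and Bonferroni for 10 comparisons. Without an effect size or SD this can only be solved backwards (two-sided assumed):
- at 0.05/10 = 0.005: d = (2.807 + 1.036) × √(2/34) = 0.93
- at 0.05: d = (1.960 + 1.036) × √(2/34) = 0.73

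The figure is neither confirmed nor refuted. It does show that d = 0.7 is not an extreme choice for what follows.

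**2. Month-6 ANCOVA, all three active arms better than control by d.** The squared deviations of the arm means sum to 3(0.25d)² + (0.75d)² = 0.75d². Residual variance given baseline is 1 − r². With d = 0.7 and r = 0.5:
- λ = 42 × 0.75 × 0.49 / 0.75 = 20.58
- error df = 168 − 5 = 163; critical F(3, 163) = 2.66
- power = 0.976, about 98%

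**3. Gate with post-baseline levels only.** With two such visits the interaction is a test of the between-visit difference across arms. For a stable effect the arm difference is d − d = 0, so λ = 0 and the gate passes 5% of the time whatever d is. Simulation with d of 0.5, 0.73 and 0.93 and r of 0.5 and 0.8 (1,000 trials each) gave 4–6% throughout.

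The loss is not confined to a perfectly flat effect. With r = 0.5 the between-visit difference has variance 2(1 − 0.5) = 1:
- effect growing from 0.5 to 0.7 SD: λ = 42 × 0.75 × 0.2² = 1.26, power about 13%
- effect growing from 0.35 to 0.7 SD: λ = 42 × 0.75 × 0.35² = 3.86, power about 34%
- only the combined arm effective, half the effect lost by month 12: about 20% (d 0.5, r 0.5) to 95% (d 0.93, r 0.8), against 78% to 100% for month-6 ANCOVA

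**4. Gate with baseline also a level.** For levels {0, 6} the model is y6 − y0 = a + b·y0 + arm. Moving y0 across gives y6 = a + (b + 1)·y0 + arm. The arm terms, residuals and F are the same as in the month-6 ANCOVA. In simulation at d 0.5, r 0.5, both reject 78% of the time. For levels {0, 6, 12} a stable effect is detected 85% of the time, so again nothing is lost.

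**5. Cost of an overall gate placed before Bonferroni.** Combined arm at 0.7 SD, single arms at 0.35 SD, 42 per arm, uninformative baseline:

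| Bonferroni divisor | Direct contrast | With overall gate |
|---|---|---|
| 3 | 78.9% | 73.5% |
| 6 | 70.7% | 69.6% |
| 10 (the count in Sample size estimation) | 64.4% | 64.4% |

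**6. Randomisation blocks.** Randomization methods says: "10 blocks of 20 randomization numbers will be generated and sealed in an envelope". With assumed block ICCs of 0, 0.05, 0.1 and 0.2, ignoring blocks gives type I error of 4.7%, 4.7%, 3.9% and 3.3%. Power at d = 0.5 is 71%, 71%, 72% and 74% ignoring blocks, against 70%, 73%, 75% and 81% adjusting for them.

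**The case against.** The strongest reply is that the failure depends on a reading the article does not state. Liver fat is the outcome the power statement addresses. On the Primary outcomes schedule it has only baseline and month 6, so the interaction test is exactly the ANCOVA one would recommend. Liver fat has no month-3 value on either schedule, so an effect held from month 3 to month 6 cannot be missed for it. That stands, and it limits the problem to microbiota at months 3 and 6, and to liver fat if months 6 and 12 are the levels.

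It can also be said that the percentage-change ANCOVA tests a stable 6-month effect without the interaction gate. This stands only in part. Compliance is determined after randomisation, so a model built on it is not a clean randomised comparison, and it has its own overall gate.

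Three stronger readings are tempting, and the document does not support them:

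- **The gate always costs power.** It costs about 5 points at a divisor of 3 in the scenario shown, and nothing at the divisor of 10 that the article states.
- **The intention-to-treat analysis excludes dropouts.** Sample size estimation says "We also taking into account the compliance and drop-out (15%)", and classical repeated-measures ANCOVA uses complete rows. But no complete-case rule is stated, and a missing-data rule may sit in the full protocol or analysis plan.
- **Leaving out block and sex is an error.** Ignoring blocks does not inflate type I error, and the covariate list may be detailed elsewhere.

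**Conclusion.** The concern holds as a conditional one. The article fixes a gate but not the factor on which it depends. With post-baseline levels only, a stable effect passes about 5% of the time against about 98% for month-6 ANCOVA; with baseline among the levels, there is no loss. The two schedules in the article do not settle which reading applies, and the undefined term *baseline difference* does not help. The 98% rests on an assumed 0.7 SD, correlation 0.5 and 42 per arm. The 5% does not depend on the effect size or the correlation, only on the effect being the same at both visits. Because one permissible reading can block the primary comparisons at the null rejection rate, the rule should be changed before analysis. The matters of drop-out, blocks and sex do not carry this conclusion.

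**What to change.** - For each primary outcome, make the baseline-adjusted month-6 contrast of each active arm against control the direct, Bonferroni-controlled test, on the log scale where needed. State the divisor.
- Remove the group-by-time gate.
- For outcomes with 3- and 6-month values, fit a mixed model with arm × visit and take the month-6 contrast as the test.
- Replace *baseline difference* by *baseline value*.
- Reconcile the liver-fat visits in Primary outcomes with those in the follow-up visits item, and the blood and faecal sampling visits likewise.
- Optional: add randomisation block and sex. This uses 9 + 1 = 10 of about 163 error df. For block it changes power by about −1 to +7 points over assumed ICCs of 0 to 0.2.

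The cost is analysis wording only. No new measurement is needed for the month-6 contrasts.

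### Holm step-down would be a cheap, optional replacement for the valid Bonferroni step on the three contrasts against control; its gain depends on effect sizes the protocol does not state

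*Protocol article*

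**What the plan says.** The Statistical methods section of the protocol article plans an intention-to-treat analysis to "compare the AEx, LCh and AEx + LCh groups to Con group", using a repeated-measures ANCOVA. If the group × time interaction reaches p < 0.05, "the effect will be localized utilizing Bonferroni for multiple comparisons". The size of the Bonferroni family is not stated there. Later in the same paragraph, after the percentage-change analysis, a difference is declared significant when its 95% CI excludes zero. The text does not say whether that interval is adjusted.

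The Sample size estimation section also uses Bonferroni, for a larger family: "We set the significance level at 0.05 and allowed for 10 mean comparisons with the Bonferroni correction between the groups". It states that "34 subjects in each group would have 85% power for mean comparison between the randomized groups for the liver fat", attributes this to a pilot study, and gives neither an effect size nor an SD. It then raises the number to 50 per group and mentions 15% for compliance and drop-out.

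The Discussion expects both exercise and diet to work, and the combination to work better than either alone.

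**The concern.** With three contrasts, single-step Bonferroni tests each at 0.05/3 = 0.0167, whatever happens to the other two. Holm tests the smallest p-value at 0.0167, the next at 0.025 and the last at 0.05, and stops at the first failure. It controls the family-wise error under any dependence, including the dependence created by the shared control arm.

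The difference shows when several effects are real and unequal, which is what the Discussion expects. Once the combination is rejected, the single-component arms face an easier threshold under Holm but not under Bonferroni. The contrasts at stake are therefore exercise alone and diet alone. If they are missed while the combination is found, readers may be tempted to conclude that only the combination works, although the plan does not prescribe that inference.

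**Working it through.** **Inputs from the protocol.** Four randomized arms, 50 per arm (Randomization methods); 15% for compliance and drop-out, 85% power with 34 per group, alpha 0.05 with Bonferroni for 10 (Sample size estimation); three contrasts against control after an interaction gate at 0.05 (Statistical methods).

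**Assumptions.** Two-sided tests; 50 × 0.85 = 42.5, taken as 42 evaluable per arm; common SD; family of three. All effect sizes below are assumed.

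**The plan's own figure.** The 34 per group cannot be reproduced, because no effect size or SD is given. It can only be solved backwards at 0.05/10 = 0.005 per comparison:

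d = √(2/34) × (z₀.₉₉₇₅ + z₀.₈₅) = 0.2425 × (2.807 + 1.036) = 0.93 SD.

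Had no correction been applied, d = 0.2425 × (1.960 + 1.036) = 0.73 SD.

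**Bonferroni at the implied effect, by formula.** With 42 per arm, d√(n/2) = 0.932 × √21 = 4.27.
- At 0.05/3 the critical value is 2.39, so power is Φ(4.27 − 2.39) = 97.0%.
- At 0.05/10 it is Φ(4.27 − 2.81) = 92.9%.

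Both exceed the 85% target.

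**Bonferroni against Holm, by simulation.** Four arms, pooled-variance t contrasts sharing one control, an overall F test at 0.05 standing in for the interaction gate, 100,000 runs, 42 per arm. Effects are in the order AEx / LCh / AEx + LCh. Each cell gives Bonferroni, then Holm.

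| True effects (SD) | Power, each single-component contrast | All three shown |
|---|---|---|
| 0.93 / 0.93 / 0.93 | 96.6%, 98.5% | 92%, 97% |
| 0.73 / 0.73 / 0.93 | 82%, 89% | 71%, 84% |
| 0.6 / 0.6 / 0.9 | 63%, 74% | 47%, 65% |
| 0.5 / 0.5 / 0.8 | 45%, 56% | 28%, 45% |

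- **At least one rejection:** identical under both methods, because the first Holm step is the Bonferroni test (99.6% for both in the first row).
- **No true effect in any arm:** family-wise error is about 3.0% for both with the gate, and 4.4% for both without it.
- **50 evaluable per arm, all at 0.93 SD:** 98.7% against 99.5% per contrast.
- **Only one arm works, at 0.93 SD, 42 per arm:** 96.7% against 96.8%.

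**Agreement with intervals.** A Bonferroni-adjusted CI excludes zero exactly when Bonferroni rejects. Every additional Holm rejection is therefore a contrast whose Bonferroni-adjusted CI includes zero. At 0.6/0.6/0.9 SD this affects at least one contrast in about 20% of trials.

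**The case against.** The strongest reply is that nothing here is wrong. Bonferroni is valid and prespecified, and its cost was budgeted at sizing for ten comparisons, more than the three contrasts need. At the only effect that the sizing implies, Holm adds about 2 points per contrast and nothing to the chance of finding some effect. The larger gains come from effect sizes that the protocol does not contain. Bonferroni also has matching simultaneous intervals, which suits a plan that reads significance from CIs; Holm has no equally simple ones. Finally, the family of three is an inference, since Statistical methods does not state its size.

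Most of this stands. A reader might infer that the plan gives up clear power for nothing. The documents do not support that: the power loss depends on unstated effects, and Bonferroni provides matching intervals in return.

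Two parts are weaker. The 0.93 SD is itself back-solved, and giving it to every arm does not fit the Discussion's expectation that the combination is stronger. And the interval argument is incomplete, because the protocol does not say that its 95% CIs are adjusted; unadjusted ones would not match Bonferroni decisions either.

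**Conclusion.** An optional, low-cost improvement, not the correction of an error. For the three contrasts against control, Holm is never less powerful than Bonferroni at the same family-wise error. The gain per single-component contrast is about 2 points if all arms have 0.93 SD, and about 7 to 11 points in the assumed scenarios where exercise alone and diet alone are weaker than the combination. The chance of showing all three rises by 5 points (92% to 97%) in the first case and by 13 to 18 points in the others (71% to 84%; 47% to 65%).

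These figures rest on 42 evaluable per arm, a family of three, assumed effects, and an F test in place of the interaction gate. The simulation compares means at one time point and does not model the planned baseline-adjusted repeated-measures ANCOVA.

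**What to change.** For the main group × time analysis, state that the family is the three contrasts of AEx, LCh and AEx + LCh against control, that they are tested by Holm step-down, and that significance is read from Holm-adjusted p-values. Make this change before unblinding.

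The sentence that takes significance from the 95% CI must be amended as well, so that it does not override the Holm decision. If Bonferroni-adjusted intervals are displayed, label them as such.

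The cost is a few sentences in Statistical methods and no new data. The real downside is presentational: a contrast can be Holm-significant while its Bonferroni-adjusted CI includes zero, and the report must explain this. If exact agreement between tests and intervals matters more to the sponsor than the extra power, keeping Bonferroni is defensible, provided that the family size and the adjustment of the intervals are stated.
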